### ***Randomization***

Women who are distressed (score  $\geq 7$  on the distress thermometer) (N=324) will be included in the randomized controlled trial and randomized in a computer-generated sequence of 1:1 to the intervention or control group, with stratification by age ( $< 60$  and  $> 60$  years), generating a balanced number of random assignments to the two groups in blocks of randomly varying sizes of six, eight or ten patients securing an equal distribution of patients in both groups. The randomization is blinded. Thus, neither the investigators nor the patients can influence the group to which each patient is allocated. An electronic platform will be developed by an experienced IT consultant company, to register, randomize and track included patients. The same platform will be used for the intervention activities and data collection.

Immediately after randomization, the nurse will inform patients about group allocation and consequences for further study participation. The nurse will schedule the first appointment with the patients in the intervention group.

Women who are not distressed (score  $< 7$ ) (N=432), will participate in an observational group following the same procedure as the control group.

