### **DATA COLLECTION**

#### *Questionnaires*

Both the intervention and the control group will be assessed before surgery (T1) and 1 week (T2), 6 months (T5) and 12 months (T6) and 18 months (T7) after surgery. Patients randomized to the intervention group will also be assessed at 2 months (T3) and 4 months (T4). Patients who were not distressed (score < 7 on the distress thermometer) at T1 will be excluded from the trial but will be followed longitudinally in a sub-study by filling in questionnaires and with the same follow-up assessments as the control group. The questionnaires allow assessment of the primary and secondary outcomes and also covariates and mechanisms. The baseline questionnaire will be paper-based and filled out in the clinic. The follow-up questionnaires will be electronic and a secured link will be sent to the patient's e-mail address. The electronic platform will manage questionnaire invitations and reminders.

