**Figure 2. Data collection instruments**

| Outcome            | Scale                   | Baseline before surgery | 3 week screening | 10 week screening | 18 week screening | 6 months follow-up | 12 months follow-up | 18 months follow-up |
|--------------------|-------------------------|-------------------------|------------------|-------------------|-------------------|--------------------|---------------------|---------------------|
| Demographics       | Single items            | X                       |                  |                   |                   |                    |                     |                     |
| Social support     | MOS                     | X                       |                  |                   |                   |                    |                     |                     |
| Distress           | DT                      | X                       | X                | X                 | X                 | X                  | X                   | X                   |
| Anxiety            | GAD 7                   | X                       | X                | X                 | X                 | X                  | X                   | X                   |
| Depression         | PHQ 9                   | X                       | X                | X                 | X                 | X                  | X                   | X                   |
| Symptoms           | FACT-B                  | X                       | X                | X                 | X                 | X                  | X                   | X                   |
| Physical function  | Physical function scale | X                       | X                | X                 | X                 | X                  |                     | X                   |
| Self-efficacy      | PAM                     | X                       |                  |                   |                   | X                  | X                   | X                   |
| Fear of recurrence | CARQ                    |                         |                  |                   |                   | X                  | X                   | X                   |
| Pain               | Single items            | X                       |                  |                   |                   | X                  | X                   | X                   |

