## STATISTICAL ANALYSES

Descriptive analyses will provide information on inclusion, feasibility, including participation in intervention components and data collection, satisfaction with the intervention, and information on nurse management of symptoms from medical records. Analyses will be based on intention-to-treat, with t tests to compare mean differences in change in each group between baseline and 6, 12 and 18 months of follow-up and with mixed models including all follow-ups. Primary analyses will test the effect of the intervention on distress, and secondary analyses will test for psychological symptoms, physical symptoms, and health behaviour (smoking, alcohol, BMI, physical activity). The effect of the intervention in the control and the intervention group will be assumed to be normally distributed and will be tested by the F-test. In all analyses, 99% confidence intervals will be calculated. Analyses will be performed based on the intention to treat principle including all participants and in sensitivity analyses, imputations of missing data will be performed using the last-observation-carried-forward method (28). In analyses aiming to describe the clinical impact of the intervention, we will estimate how many percent of the cases of distress, anxiety, depression and physical symptoms in the intervention versus the control group will be moved to non-cases. Furthermore, in cost-utility analyses, we will apply quality adjusted life years (QALY) to weigh the life expectancy of a patient against the Euro Quality of Life 5-Dimensions Classification (5Q-5D). Using incremental analyses, mean differences in costs (health care +disability + productivity loss + intervention) are compared with mean differences in health consequences for the intervention versus the control group.

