**Figure 3. Percentage of women changing from cases to non-cases in intervention and control group**

| Control group (%) | Intervention group (%) |
|-------------------|------------------------|
|-------------------|------------------------|

|                         |    |    |
|-------------------------|----|----|
| Distress ( $\geq 7$ )   | 61 | 90 |
| Anxiety ( $\geq 8$ )    | 53 | 80 |
| Depression ( $\geq 8$ ) | 44 | 49 |

Conservatively, we expect slightly lowered differences in change from case to non-case in the large full-scale study (20 %), compared to those observed in the pilot study (30%).

In a 2-year period, we expect 948 women to fulfill the inclusion criteria. With an expected participation rate of 80% (85% was reached in the pilot study) 758 will participate. Of these 43% will have high distress (N=324) and will enter the RCT. 57% will have low distress (n=432) and will be invited to participate in observation group who will fill-out questionnaires.

Due to a large number of planned analyses in the RCT study, we assume a highly conservative alpha to be 1%. Within a 2-year inclusion period, we will include 324 patients and an estimated 20% will drop-out or have missing data, resulting in final sample of 260.

With 130 women in each group, an expected 61% women move from cases to non-cases on distress in the control group and 81% percent women move from cases to non-cases on distress in the intervention group, we will obtain 84% power. Similar calculations for anxiety and depression reveals power of 78% and 76%.

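### The LOCF sensitivity analysis can carry a 1-week distress value in controls but a 2- or 4-month value in the intervention arm, so it cannot show robustness to dropout

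*Protocol*

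**What the plan says.** Three parts of the Protocol bear on this.

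- **Statistical analyses.** The main comparisons are "t tests to compare mean differences in change in each group between baseline and 6, 12 and 18 months of follow-up", together with mixed models. For missing data, "in sensitivity analyses, imputations of missing data will be performed using the last-observation-carried-forward method (28"). No other imputation method is named, and nothing limits which visits may supply the carried value.
- **Questionnaires (Data collection).** "Both the intervention and the control group will be assessed before surgery" (T1), and again at 1 week (T2), 6 months (T5), 12 months (T6) and 18 months (T7). Then: "Patients randomized to the intervention group will also be assessed at 2 months" (T3) and at 4 months (T4). Controls have no visit between 1 week and 6 months.
- **Power and participation.** Of 324 randomized women, "an estimated 20% will drop-out or have missing data, resulting in final sample of 260". The timing of the loss is not given.

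Figure 2 marks the distress thermometer at all seven time points ("Distress | DT | X | X | X | X | X | X | X"). It does not separate the arms, and it labels the early visits 3, 10 and 18 weeks. On either labelling, the Questionnaires text gives the two middle visits to the intervention arm only.

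**The concern.** LOCF puts an old value in place of a missing one. When both arms have the same visits, the replacement is equally old in both. Here it need not be. For two women who both complete T2 and are both missing at 6 months, the control's replacement dates from 1 week after surgery, while the intervention patient's may date from 2 or 4 months.

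Any change in distress over that interval then appears as a difference between arms. Two features of the Protocol make a fall plausible: every randomized woman scores 7 or more at entry, and 61% of controls are expected to become non-cases. Under a fall, LOCF credits intervention dropouts with a natural recovery that it withholds from control dropouts.

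At stake is the purpose of the analysis. It is the only check on missing data that the Protocol names, and about one woman in five is expected to be lost or incomplete. If it leans towards the intervention, its agreement with the main result is not evidence of robustness.

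**Working it through.** **The plan's own figure.** With 130 per group, 61% versus 81%, and two-sided alpha 1% (the sidedness is not stated):

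Power = Φ{[0.20 − 2.576 × √(2 × 0.71 × 0.29 / 130)] / √(0.61 × 0.39 / 130 + 0.81 × 0.19 / 130)} = Φ{(0.200 − 0.145) / 0.0549} = Φ(1.00) = 84.2%.

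The Protocol states 84%, so it is reproduced. Also 324 × 0.8 = 259.2, stated as 260, and 324 / 2 = 162 per arm.

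**Which value LOCF uses for the 6-month visit**

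| Last visit completed before 6 months | Control carries | Intervention carries |
|---|---|---|
| T1 only | T1 | T1 |
| T2 | T2 (1 week) | T2 (1 week) |
| T3 (intervention arm only) | no such visit | T3 (2 months) |
| T4 (intervention arm only) | no such visit | T4 (4 months) |

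A control who is still taking part at 4 months sits in the T2 row, because she was never asked in between. A woman lost after the 6-month visit carries a common visit in either arm.

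**Size on the mean score.** From the Protocol: 162 per arm, alpha 1%, 20% missing. Assumed, because the document gives no figure: no treatment effect, equal dropout in both arms, all 20% already missing at 6 months, every control loss after T2, SD 2.5, dropouts with the same average course as everyone else, and a fall of 1 to 2 points between T2 and T4.

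- Spurious benefit = share missing × share of intervention losses that carry T4 × fall from T2 to T4
- SE = 2.5 × √(2/162) = 0.278
- Rejection rate = P(|Z + benefit/SE| > 2.576)

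| Intervention losses after T4 | Fall | Spurious benefit | Benefit/SE | Rejection rate at nominal 1% |
|---|---|---|---|---|
| All | 1 | 0.2 × 1 × 1 = 0.2 | 0.72 | 3.2% |
| All | 2 | 0.2 × 1 × 2 = 0.4 | 1.44 | 12.8% |
| Half (rest before T3) | 1 | 0.2 × 0.5 × 1 = 0.1 | 0.36 | 1.5% |
| Half (rest before T3) | 2 | 0.2 × 0.5 × 2 = 0.2 | 0.72 | 3.2% |

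**Size on case to non-case.** Assume both arms are truly 61% non-case at 6 months, controls carry T2 and intervention women carry T4. The spurious difference is the share missing × (non-case share at T4 − non-case share at T2).

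- 20% missing, 40% non-case at T2, 61% at T4: 0.20 × 0.21 = 4.2 points, rejection rate 3.6%.
- 10% missing, 20% at T2, 61% at T4: 0.10 × 0.41 = 4.1 points, 3.4%.
- 5% missing, 20% at T2, 61% at T4: 0.05 × 0.41 = 2.0 points (rounded), 1.6%.
- 20% missing, 70% at T2, 61% at T4: 0.20 × (−0.09) = −1.8 points. The sign reverses.

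**With common visits only.** Both arms carry T2 or T1. With equal dropout and no effect the spurious difference is 0 and the rejection rate is 1%.

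**The case against.** **It is only a sensitivity analysis.** This stands. The main t tests and the mixed models do not carry values forward. The rejection rates above belong to a supporting analysis and are not the trial's type I error. A reader might infer that the primary result is biased, but the Protocol does not support that.

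**The direction is not established.** This stands in part. The 61% recovery is measured from case status and has no stated time point. Regression to the mean after selection at 7 or more may already be visible at 1 week, which both arms have. Oncological treatment follows surgery, so distress over the interval could move either way. The direction is therefore conditional, but the difference in the age of the carried values is not.

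**The size depends on when women are lost.** This stands, and it is why the lower range is shown. Placing the whole 20% before 6 months, with every intervention loss after T4, is the upper end.

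**A stronger reading is tempting.** One could argue that carried control values are always cases, because entry requires 7 or more, and so obtain a spurious case to non-case difference of 10 points or more. That would need every lost control to miss the 1-week visit while every lost intervention patient still reports at 4 months. It builds in different dropout timing by arm, which the Protocol does not suggest. Women with only T1 are carried as cases in both arms, so they create no asymmetry.

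**An SAP could limit the visits used.** It could, and none is shown. But the Protocol does not merely leave the matter open: it names the method and sets the unequal schedule, and followed as written the two conflict.

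**Conclusion.** The point holds as a should-fix. As written, LOCF draws on values of different age in the two arms for women who complete the 1-week visit and lack the 6-month value. It does not touch the main analyses, women lost after 6 months, or women with only the pre-surgery value. It concerns only measures also taken at T3 and T4: distress, GAD-7, PHQ-9, FACT-B and physical function.

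If distress falls by 1 to 2 points between 1 week and 4 months, the spurious benefit with no true effect lies between 0.1 and 0.4 points, and the rejection rate at nominal 1% is about 1.5% to 13%, depending on when intervention patients are lost. These figures rest on an assumed SD of 2.5, 20% missing by 6 months, and equal dropout. A smaller loss before 6 months gives a smaller bias, and higher distress at 4 months than at 1 week would reverse the sign. In every case except no change over the interval, the analysis mixes the passage of time with treatment, so it cannot serve as a check on the expected 20% loss.

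**What to change.** Do not carry T3 or T4 values forward in one arm only. Preferably, replace LOCF with multiple imputation using baseline covariates and the visits common to both arms (T1, T2, T5, T6, T7), and add a delta-adjusted analysis to examine data missing not at random. At the least, keep LOCF but state that only those common visits may supply the carried value. That removes the asymmetry but leaves LOCF's general weaknesses, such as treating imputed values as observed.

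The cost is a change of wording and a little programming. No new data are needed. The change should be made before outcome data are analysed by arm.

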#### *Patient reported outcome measures*

PROMs screening for psychological and physical symptoms will be performed before surgery (T1) and 1 week (T2), 2 months (T3) and 4 months (T4) after surgery. A positive PROMs screening includes above-normal scores on the distress thermometer or the Functional Assessment of Cancer Therapy –Breast (FACT-B) symptom inventory at any of the four assessments or indicating health behaviour that is not in accordance with recommendations (daily smoking, alcohol consumption of  $\geq 7$  units per week, body mass index  $\geq 25$  or physical inactivity  $< 150$  min/week + 20 min intensive recreational training x 2/week) at baseline only (Appendix 7). A positive screening will inform the nurse navigator and the dialogue between the patient and the nurse navigator. However, no fixed actions will be taken based on a positive screening. The PROM symptoms will be reported through the project electronic platform. The results of the PROMs will be available to the nurse where symptoms are categorized as a traffic light with green indicating low symptoms, yellow indicating moderate symptoms with nurse evaluating is necessary and red light indicating immediate nurse evaluation.

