#### *Nurse navigation*

Nurse navigation includes individual counseling and psycho-education (e.g. understanding the cancer diagnosis and the treatment) to motivate and support patients in self-managing their symptoms, and, if relevant, use existing rehabilitation services at the hospital (surgery,

[figure not shown]

oncology, radiotherapy departments) or at the local rehabilitation centers. In Denmark, cancer rehabilitation is provided by the local municipalities' rehabilitation centers with great variations in terms of rehabilitation services. The nurse navigator will advise the patient on the different opportunities and referral could e.g. be to an oncology nurse for management of pain or nausea, referral to the local health center for management of psychological distress in support groups or for physical exercise to alleviate arm and shoulder problems (Appendix 8). The nurse navigator may furthermore refer the patient to up to six project-funded individual sessions with a project psychologist.

Up to six individual, manual-based, face-to-face or telephone sessions are offered, depending on individual needs (Appendix 9). Each session includes: 1) emphatic listening and dialogue, 2) collaborative empiricism (patient's private world and navigator's professional standards), 3) thorough assessment of needs, 4) psychoeducation, 5) goal setting, 6) intervention –agreements and plan, 7) debriefing and 8) session evaluation using the Session Rating Scale SRS based on Feed-back Informed Treatment. Two nurses ([name] and to-be-named) will be trained to function as nurse navigators. We have, based on experiences from the pilot study decided to apply the instrument Session Rating Scale (SRS) (13) developed in The Client Directed Outcome Informed (CDOI) psychotherapy approach to identify patient tracks with no or negative improvement in order to optimally adjust the care to patient resources, goals, ideas for change and experience of the care collaboration (Appendix 9).

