### Outcomes

Data collection instruments used to measure the individual outcomes are illustrated in Figure 2 and items for all questionnaires are shown in Appendix 10. The primary outcome is psychological distress, defined as a multifactorial, unpleasant psychological (cognitive, behavioural, emotional), social or spiritual emotional experience that potentially influences the ability to manage the cancer disease, symptoms and treatment. This will be measured using the distress thermometer. Secondary outcomes include anxiety and depression, breast cancer specific psychological and physical symptoms, quality of life measure to obtain cost-utility, health behaviour (smoking, alcohol consumption, body mass index and physical activity), fear of recurrence, social support, unmet needs, and acceptability. Feasibility outcomes will include indicators of whether the intervention has had an effect on the mechanisms and will include patient activation.

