| Neuropathy         | Single items            | X                       |                  |                   |                   | X                  | X                   | X                   |

|                    |              |   |  |  |  |   |   |   |
|--------------------|--------------|---|--|--|--|---|---|---|
| Sleep              | PSQI         | X |  |  |  | X | X | X |
| Cognitive function | FACT-cog     | X |  |  |  | X | X | X |
| Health behavior    | Single items | X |  |  |  |   |   | X |
| Need for support   | Single items | X |  |  |  | X | X | X |
| Quality of life    | EQ-5D        | X |  |  |  |   |   | X |
| Acceptability      | Single items |   |  |  |  |   |   | X |

Note. MOS Medical Outcomes Study Social Support Survey (17). DT Distress thermometer (18,19). GAD 7 Generalized Anxiety Disorder (20). PHQ 9 (depression) The Patient Health Questionnaire (21). FACT-B Functional Assessment of Cancer Therapy –Breast (22). Physical Function Scale (29). PAM Patient Activation Measure (23). CARQ Fear of Recurrence (24). Pain (single items), neuropathy (single items). PSQI Pittsburgh Sleep Quality Index (25). FACT-cog Functional Assessment of Cancer Therapy-Cognitive (26). Health behavior including smoking, alcohol, physical activity, BMI (single items). Need for support (single items). EQ-5D Euro Quality of Life-5-Dimensional Classification (27).

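### EQ-5D is scheduled only before surgery and at 18 months, so the QALY difference between arms rests on a utility course that is not observed in between

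*Protocol*

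**What the plan says.** The Outcomes section of the protocol lists among the secondary outcomes a "quality of life measure to obtain cost-utility". The Statistical analyses section makes EQ-5D the basis of the QALYs: "in cost-utility analyses, we will apply quality adjusted life years (QALY) to weigh the life expectancy of a patient against" the EQ-5D. It then sets costs against effects: "mean differences in costs (health care +disability + productivity loss + intervention) are compared with mean differences in health consequences".

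Figure 2 fixes the schedule. Its last three columns are "6 months follow-up | 12 months follow-up | 18 months follow-up", and the EQ-5D row reads "Quality of life | EQ-5D | X | | | | | | X". The instrument is therefore marked before surgery and at 18 months, and all five cells in between are empty.

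The same figure marks distress, anxiety, depression, FACT-B, patient activation, pain and sleep at 6 and 12 months as well. The Questionnaires section confirms that both arms are assessed at those visits. The symptom screening that informs the nurse sessions "will be performed before surgery (T1) and 1 week (T2), 2 months (T3) and 4 months (T4) after surgery". On the cost side, the Nurse navigation section says: "Up to six individual, manual-based, face-to-face or telephone sessions are offered, depending on individual needs". The nurse may also "refer the patient to up to six project-funded individual sessions with a project psychologist".

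**The concern.** A QALY is utility accumulated over time, so the path between the first and last measurement matters as much as the end points. Here the path is measured at its two ends only. The screening that feeds the intervention ends about 4 months after surgery, so a difference in utility could well appear early. The protocol tests the clinical outcomes at 6, 12 and 18 months, but the utility measure skips the first two of these.

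At stake is the credibility of the cost-utility result. The Dissemination section plans a paper on the price of nurse navigation. The Perspectives section makes support for implementation in other departments conditional partly on promising cost-effectiveness.

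The schedule also leaves no fallback: a woman who does not return the 18-month form has no EQ-5D value after baseline. The protocol expects 20% drop-out or missing data overall.

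**Working it through.** The protocol gives no QALY, utility or cost figure, so there is none to reproduce. The check is how much the planned schedule can differ from one that also uses the existing 6- and 12-month visits.

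**Inputs from the protocol.** EQ-5D at 0 and 18 months (Figure 2). Questionnaires in both arms at 6, 12 and 18 months (Questionnaires section, Figure 2).

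**Assumptions, not in the protocol.** Linear interpolation between measurements. The pre-surgery value counts as time 0. The arms do not differ at baseline. The utility gains are illustrative, around 0.05, with a range of 0.03 to 0.10.

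**Formulas.** Let d0, d6, d12 and d18 be the difference in mean utility between arms at each visit, with time in years.

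- Planned, two points: 1.5 × (d0 + d18)/2 = 0.75·d0 + 0.75·d18.
- Four points, 0.5 years apart: 0.25·d0 + 0.5·d6 + 0.5·d12 + 0.25·d18.
- Two-point minus four-point: 0.5·(d0 + d18 − d6 − d12).

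Under the planned schedule d6 and d12 carry no weight. With d0 = 0, the two-point result is too low when d18 is less than d6 + d12, correct when they are equal, and too high when d18 is greater.

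**Results with d0 = 0.**

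| Pattern | d6 | d12 | d18 | Four points | Two points | Two as share of four |
|---|---|---|---|---|---|---|
| Gone by 18 months | 0.05 | 0.03 | 0 | 0.025 + 0.015 + 0 = 0.040 | 0 | 0% |
| Fading | 0.05 | 0.03 | 0.01 | 0.025 + 0.015 + 0.0025 = 0.0425 | 0.0075 | 18% |
| Constant from 6 months | 0.05 | 0.05 | 0.05 | 0.025 + 0.025 + 0.0125 = 0.0625 | 0.0375 | 60% |
| Linear rise | 0.0167 | 0.0333 | 0.05 | 0.0083 + 0.0167 + 0.0125 = 0.0375 | 0.0375 | 100% |
| Only at 18 months | 0 | 0 | 0.05 | 0 + 0 + 0.0125 = 0.0125 | 0.0375 | 300% |

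**Range.** The results scale with the size of the gain, so the shares do not change. For a largest gain of 0.03 to 0.10:

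- Gone by 18 months: 0.024 to 0.080 with four points, 0 with two.
- Constant: 0.0375 to 0.125 with four, 0.0225 to 0.075 with two.
- Only at 18 months: 0.0075 to 0.025 with four, 0.0225 to 0.075 with two.

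**Baseline.** The formulas also give d0 a weight of 0.75 with two points and 0.25 with four. A chance difference in pre-surgery utility therefore counts three times as much under the planned schedule, unless it is adjusted for.

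The four-point figure is a better reference but not the truth, because it still interpolates over the first 6 months.

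**The case against.** A reader might infer that the schedule cannot register any benefit at 6 or 12 months while every intervention cost is charged, so that the trial is bound to report added cost for little gain. The documents do not support that, for four reasons.

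- A difference still present at 18 months earns credit for the period before it: 60% if constant from 6 months, all of it if it rises linearly. Full loss needs a benefit that has gone by 18 months, and the protocol gives no time course for utility.
- The error is not one-directional. A late difference is overstated.
- The cost side includes health care, disability and productivity loss, taken from registries, municipal rehabilitation centers and medical records. Early savings there would be counted in full, whatever the EQ-5D schedule.
- The implementation offer depends first on effects on psychological and physical symptoms, and only in addition on cost-effectiveness.

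These objections stand, and they limit the point to an unobserved trajectory.

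It can also be said that linear interpolation is not in the protocol, and that a statistical or health-economic plan not shown here may define the QALY calculation. FACT-B, anxiety and depression scores at 6 and 12 months might be used to estimate intermediate utilities. That is fair, and the absence of a QALY formula from the protocol is not held against it. But the protocol names no such mapping, and no later plan can supply EQ-5D values that were never collected.

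Finally, the life-expectancy phrase could be read as a plan to weight by a quantity that 18 months of follow-up does not observe. It reads more naturally as a loose definition of a QALY, so it calls for clarification at most.

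**Conclusion.** The point holds as a cheap improvement to the design. EQ-5D is the only named utility source, it is measured only at the two ends of follow-up, and the QALY difference between arms therefore depends on a course that is not observed. That much follows from Figure 2 and the Statistical analyses section without further assumptions.

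The size does rest on assumptions, namely linear interpolation and illustrative gains. On these, the planned schedule can miss a benefit altogether, credit it in part, get it right, or triple it, according to the pattern over time. No systematic loss is shown. The primary outcome, its power and the analyses of symptoms are not affected.

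**What to change.** Add EQ-5D to the 6- and 12-month questionnaires in both arms and mark those cells in Figure 2. Compute QALYs as the area under the utility curve over the 18-month follow-up, adjusted for baseline utility; this definition may sit in the statistical or health-economic plan. Reword the sentence on life expectancy in the Statistical analyses section so that the time horizon is clear.

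The cost is five extra items on two electronic questionnaires that are already sent, a slight burden for patients, and a minor amendment.

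If collection can no longer be changed, state the interpolation or mapping to be used, report how the result varies over plausible trajectories in both directions, and name the limitation in the cost paper.
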